## Abstract

**Background:**

Metformin is a biguanide oral hypoglycaemic agent commonly used for the treatment of type 2 diabetes mellitus. In addition to its anti-diabetic effect, metformin has also been associated with a reduced risk of cancer incidence of a number of solid tumours, including prostate cancer (PCa). However, the underlying biological mechanisms for these observations have not been fully characterised in PCa. One hypothesis is that the indirect insulin lowering effect may have an anti-neoplastic action as elevated insulin and insulin like growth factor − 1 (IGF-1) levels play a role in PCa development and progression. In addition, metformin is a potent activator of activated protein kinase (AMPK) which in turn inhibits the mammalian target of rapamycin (mTOR) and other signal transduction mechanisms. These direct effects can lead to reduced cell proliferation. Given its wide availability and tolerable side effect profile, metformin represents an attractive potential therapeutic option for men with PCa. Hence, the need for a clinical trial investigating its biological mechanisms in PCa.

**Methods:**

METAL is a randomised, placebo-controlled, double-blind, window of opportunity study investigating the biological mechanism of metformin in PCa. 100 patients with newly-diagnosed, localised PCa scheduled for radical prostatectomy will be randomised 1:1 to receive metformin (1 g b.d.) or placebo for four weeks (+/− 1 week) prior to prostatectomy. Tissue will be collected from both diagnostic biopsy and prostatectomy specimens. The primary endpoint is the difference in expression levels of markers of the Fatty acid synthase (FASN)/AMPK pathway pre and post treatment between the placebo and metformin arms. Secondary endpoints include the difference in expression levels of indicators of proliferation (ki67 and TUNEL) pre and post treatment between the placebo and metformin arms. METAL is currently open to recruitment at Guy’s and St Thomas’ Hospital and the Royal Marsden Hospital, London.

**Discussion:**

This randomised placebo-controlled double blinded trial of metformin vs. placebo in men with localised PCa due to undergo radical prostatectomy, aims to elucidate the mechanism of action of metformin in PCa cells, which should then enable further larger stratification trials to take place.

**Trial registration:**

EudraCT number 2014–005193-11. Registered on September 09, 2015.

**Electronic supplementary material:**

The online version of this article (doi:10.1186/s12885-017-3458-3) contains supplementary material, which is available to authorized users.

## Background

The incidence of prostate cancer (PCa) has significantly increased over the past decades and will remain a significant health burden in years ahead. Patients presenting with localised disease at diagnosis are categorised into low, intermediate or high risk based on clinical stage, prostate specific antigen (PSA) level and histopathological Gleason score [1]. Current treatment options for men with intermediate and high risk disease include radical prostatectomy (open, laparoscopic or robotic) and radiotherapy with Neoadjuvant/adjuvant hormone therapy [2]. However, due to the risk of relapse in these groups, Neoadjuvant treatment has been investigated, but with disappointing results [3].

Type 2 Diabetes (T2DM) or impaired glucose tolerance are included in the cluster of disorders which comprise the metabolic syndrome (MetS) [4]. During the last decade, studies have investigated whether MetS is involved in the aetiology of PCa [5–7] [8, 9]. A meta-analysis to quantify the risk of PCa related to MetS found a pooled relative risk of 1.54 (95% CI:1.23–1.94) [4]. Recent studies have also suggested that the presence of MetS or some of its features is associated with higher grade disease in men with PCa and can lead to more rapid progression to castrate resistant PCa [10, 11].

Metformin (1,1-dimethylbiguanide hydrochloride) is a biguanide class of oral hypoglycaemic agent and commonly used for the treatment of T2DM. Metformin inhibits gluconeogenesis and reduces circulating levels of insulin [12]. It is also thought to play a role in lowering triglycerides and LDL cholesterol levels [13]. The usual dose is 2 g daily in divided doses and mild gastrointestinal discomfort with diarrhoea is the most common side effect (>10%). Other common side effects include: nausea, vomiting and abdominal pain. However, if dose escalation is perfomed carefully most patients are able to receive maximum drug dosing. Lactic acidosis is a very rare, but a serious adverse event [14]. To limit the risk of lactic acidosis, patients with risk factors for its development will be excluded from the study (renal impairment, hypoxia, congestive heart failure).

In addition to the anti-diabetic effect, metformin has also been associated with a reduced risk of various cancers, including PCa incidence and mortality in epidemiological studies [15–17]. However, the underlying biological mechanisms for these observations have yet to be fully characterised [18]. One hypothesis is that indirect insulin lowering effect may have an anti-neoplastic effect as elevated insulin and insulin like growth factor − 1 (IGF-1) levels play a role in prostate cancer development and progression [19]. In addition, metformin is also a potent activator of activated protein kinase (AMPK), which in turn inhibits the mammalian target of rapamycin (mTOR) and other protein synthesis. These direct effects can lead to reduced cell proliferation [20].

A recent study has evaluated the effects of metformin on PCa focusing on the AMPK pathway in paired pre-treatment and prostatectomy specimens [21]. Although the study was limited by small sample size and lack of a control arm, a change in the proliferation marker ki67 could be observed following metformin therapy (mean 50% reduction). Together with our collaborators at the Centre for Molecular Oncologic Pathology (CMOP), Dana Farber Cancer Institute (DFCI), we have also investigated the molecular pathways involved in PCa in a cohort of 181 men. Preliminary results from the Uppsala Longitudinal Study of Adult Men (ULSAM) cohort showed that men with higher levels of fatty acid synthase (FASN) had an increased risk of prostate cancer death compared to patients with normal levels (unpublished data). Furthermore, Flavin et al. have shown that lack of AMPK activity is associated with and may be an important biochemical alteration in MetS [22].

### Rationale for the study

A potential role for metformin in PCa has been suggested and given its wide availability, tolerable side effect profile and safety record it may represent a therapeutic option for men with PCa. However, the mechanism of action by which metformin exerts its anti-cancer effect has yet to be fully characterised. This ‘window of opportunity’ trial provides an opportunity to investigate this by comparing baseline prostate biopsies with post-treatment surgical specimen by focussing on assessment of the FASN/AMPK axis. This study will have a placebo arm in order to provide a control group. Non-diabetic patients with newly diagnosed PCa scheduled for radical prostatectomy will be eligible for treatment with metformin/placebo for four weeks prior to prostatectomy.

### Risk/benefit

Usual timing between diagnostic biopsy and prostatectomy is four weeks on average, so therefore it is not expected that surgery will be delayed as a result of participation in this study. Since this is a proof of principle trial with a relative short duration of treatment, it is unlikely that patients will derive significant benefit by study participation. However, it has been shown that metformin is well tolerated in a non-diabetic population [21, 23] and it is not anticipated that patients will experience increased morbidity by study participation.

### Trial design

This is a randomised, placebo-controlled, double-blind, window of opportunity study investigating the biological mechanism of metformin in PCa. Patients with newly-diagnosed, early stage, prostate cancer scheduled for radical prostatectomy will either enter the main study and be randomised 1:1 to receive metformin (2 g daily over 2 divided doses; Arm A) or placebo four weeks prior to prostatectomy (standard of care; Arm B). A subset of five patients will enter the exploratory PET-MRI sub study. These five patients will all receive metformin and will undergo an additional two PET-MRI Scans (see below).

Patients with a history of a current or historical diagnosis of diabetes mellitus and/or prior metformin use will be excluded.

The primary objective of this study is to investigate the biological mechanism of metformin on PCa using pharmacodynamic markers (Table 1). The primary endpoint for this study is the difference in expression levels of biomarkers representing the FASN/AMPK pathway for the metformin and placebo groups, as measured by the H score. Secondary endpoints include the difference in indicators of proliferation in the same groups, as well as differences in expression levels of the biomarkers between benign and malignant tissue (Table 1).

**Table 1 Tab1:** Objectives

Objectives	Endpoints
Primary endpoints	
To determine the biological effect of metformin on markers of the FASN/AMPK pathway in prostate tissue by comparison of pre and post-treatment samples.	Assessment of the difference in expression levels of markers of the FASN/AMPK pathway pre and post treatment between the placebo and metformin arms.
Secondary endpoints	
To evaluate the biological effect of metformin on markers of proliferation in prostate tissue by comparison of pre and post-treatment samples.	Assessment of the difference in expression levels of indicators of proliferation (ki67 and Terminal deoxynucleotidyl transferase dUTP nick end labelling (TUNEL)) pre and post treatment between the placebo and metformin arms.
To evaluate differences in FASN/AMPK-associated markers in benign and malignant prostate tissue.	Assessment of the difference in expression levels of markers of the FASN/AMPK pathway and indicators of proliferation between benign and malignant prostate tissue in the placebo and metformin arms.
To measure metformin levels in prostate tissue.	Assessment of the difference in metformin levels in baseline and post-treatment prostate tissue.
To determine safety of metformin in this non-diabetic patient cohort.	Assessment of adverse events and laboratory evaluations.
To determine surgical toxicity.	Assessment of surgical-specific toxicities: time between biopsy and surgery, peri-operative bleeding, infection, rectal injury and length of hospital stay.
Exploratory Objectives and Endpoints	
To evaluate the effects of metformin on functional imaging of the prostate.	Difference in ^18^F Choline PET/MRI between baseline and post-treatment (prior to prostatectomy) in a separate non-randomised cohort of five patients with MRI positive disease receiving metformin.

Following informed consent (see Additional file 1: Appendix 1 for informed consent form) and screening, patients in the main study will be randomised and continue metformin or placebo for four weeks until the evening prior to radical prostatectomy. The five patients in the PET-MRI sub study will all receive metformin. In the event that surgery is scheduled for after this time point, patient will continue study drug for an additional one week. Prostate tissue (at baseline from biopsy and post treatment from prostatectomy) will be used for analysis of p-AMPK, p-ACC, FASN by immunohistochemistry and proliferation will be measured using ki67 and TUNEL in both groups.

Tissue metformin levels will also be assessed in baseline and post-treatment prostate tissue in the metformin-cohort. Each tissue specimen will be assessed by an experienced uro-pathologist to identify benign and malignant tissue. Patients will also be invited to consent for tissue storage in an HTA licensed Biobank. Additional translational studies may be undertaken based upon the results of the initial analysis as described in this protocol. Study drug safety will be assessed by recording adverse events.

The primary endpoint of this study is pharmacodynamic and therefore time between study drug dose and prostatectomy is an important factor. To minimise the effects of dose reductions and interruptions, the primary endpoint analysis will be based on a per protocol analysis. Evaluable patients are defined as:

-Received at least 21 days (3 weeks) of study drug between 1.5–2.0 g daily.

-Received study drug uninterrupted for the last 7 days prior to prostatectomy.

-A secondary analysis will include an intention-to-treat analysis.

Histopathological staging from prostatectomy will be performed. Following prostatectomy, all patients will be followed up for a final safety assessment and recording of surgical toxicity by the Clavien-Dindo system. Following this visit, patients do not require further study-related follow up and will continue to receive standard of care.

The exploratory endpoint of this study involves 18F Choline PET/MRI evaluation at baseline and post-metformin (pre-prostatectomy) for assessment of response in prostate tissue. This exploratory sub-study will include 5 patients with MRI positive disease, not randomised in the main trial, all of whom will receive metformin. Apart from the additional two visits for the 18F Choline PET/MRI scans they will follow the same trial protocol/visit schedule as those in the main study. The criteria for enrolment in to this sub study are:Patient willing to undergo two additional PET-MRI scansMRI positive diseaseSatisfactory completion of MRI safety questionnaireAvailability of 18F Choline and scanning slots which would not result in a delay to the patient’s enrolment into the study or to their surgery

## Methods: Participants, interventions, and outcomes

### Study setting

The trial is currently open at two tertiary referral hospitals in London, UK.Guy’s and St Thomas NHS Foundation TrustRoyal Marsden NHS Foundation Trust

Full details can be found on the EudraCT website https://www.clinicaltrialsregister.eu/ctr-search/search?query=2014-005193-11.

### Eligibility criteria

#### Inclusion criteria

Patients eligible to participate in this study are those who meet all of the following inclusion criteria:Age 18 or older and willing and able to provide signed informed consent.Histologically confirmed adenocarcinoma of the prostate, with a maximal tumour length of greater or equal to 6 mm on core biopsyNo previous treatment for prostate cancer (including surgery, any hormone therapy, radiotherapy and cryotherapy)Prostate biopsy within 6 months from screeningRadical prostatectomy is the scheduled treatment of choiceEastern Cooperative Oncology Group (ECOG) Performance status less than or equal to 0 or 1Adequate organ function, defined as follows:Haemoglobin >10.0g/dLAbsolute neutrophil count >1.5x10^9^/LPlatelet count >100x10^9^/LRenal function, eGFR >60ml/min (calculated by Cockcroft Gault)AST and/or ALT <2.5 x ULNTotal Bilirubin <1.5 x ULNAble to swallow the drug and comply with study requirements.

#### Exclusion criteria

Patients must NOT meet any of the following exclusion criteria:Patients with a current or historical diagnosis of type one or two Diabetes and/or have ever received metforminPatients with hypersensitivity to any of the components of Metformin or placebo tabletHistory of or conditions associated with lactic acidosis such as shock or pulmonary insufficiency, alcoholism (acute or chronic), and conditions associated with hypoxaemiaPatients with chronic liver disease, severe cardiovascular impairment, cardiac failure, recent myocardial infarction, severe peripheral vascular disease or renal impairment (eGFR <60 ml/min as measured by Cockcroft Gault)Patients with acute severe disorders, for example infections with fever, pancreatitis, trauma, dehydration or reduced diet (<1000 kcal or 4200 kJ per day)Other active malignancy over the last five years that has required systemic therapy, excluding:Adjuvant therapy in the curative settingNon-melanoma skin cancerSuperficial transitional cell carcinoma (CIS-T1)
Current enrolment in an investigational drug or device study or participation in such a study within 30 days of signing consent.Any subjects who is able to father a child and does not agree to use barrier protection, in the form of a condom, for the duration of the trial and for 16 weeks after the last study drug administration.

### Interventions

Screening procedures within 14 days of consentWritten informed consent from all participantsClinical assessments:Complete medical history, including diagnosis, history of other diseases (active or resolved), concomitant illnesses and medications.Record of patient demographicsPhysical examination including vital signs, height and weight, waist/hip ratio and ECOG performance status
Laboratory determinations: Blood results taken within 14 days of consent for other purposes can be used as part of the screening process:Full Blood Count (FBC), renal function, liver Function Tests (LFT), bone profile, fasting glucose, PSA, testosterone, fasting lipid profile, HbA1c. Select sites will also take two additional samples for a whole blood and serum save. This will be taken according to trial specific SOP (see Additional file 2: Appendix 2).Radiological assessment:MRI Safety AssessmentIn subgroup of 5 patients with MRI positive disease receiving metformin: ^18^ F Choline PET/MRI
Tissue collection: Formalin Fixed Paraffin embedded tissue will be collected from baseline diagnostic specimen.

Study week 1 (day 1):Clinical assessments:Physical examination including ECOG performance status if greater than 7 days from screening physical examinationBaseline adverse eventsMedication reviewGiven compliance diary

Study week 3 (+/− 2 days):Clinical assessments:Physical examination, including ECOG performance status and vital signs.Adverse eventsCompliance evaluation (diary and verbal)Medication revieW

Laboratory determinations: Blood tests taken within 2 days of compliance visit for other purposes can be used as part of the compliance visitFBC, renal function, LFT, bone profile

Study week 4 (+/− 1 week) pre-prostatectomy:Clinical assessments:Physical examination, including ECOG performance status, weight, waist/hip ratio and vital signsAdverse eventsCompliance evaluationMedications review
Laboratory determinations: Blood tests taken within 2 days of surgery visit for other purposes can be used as part of the surgery visit: FBC, Renal function, LFT, bone profile, fasting glucose, PSA, testosterone, fasting lipid profile. Select sites will also take two additional samples for a whole blood and serum save. This will be taken according to trial specific SOP (see Additional file 2: Appendix 2).
Radiological assessment: In a subgroup of 5 patients with MRI positive disease: ^18^ F Choline PET/MRI, which will be performed after 21+/− 2 days of metformin and prior to prostatectomy. A time point prior to 28 days is chosen to allow radiological assessment to be scheduled without interfering with surgery scheduling.
A pre-operative surgical visit should occur prior to surgery, as per standard of care and local policies.

Study week 4 (+/− 1 week) – prostatectomy:

Patients will undergo prostatectomy. This will occur at the end of week 4 (+/− 1 week). Study drug treatment will continue up until the evening before surgery until the patient is nil by mouth (as per local guidelines). In the events patients undergo surgery beyond 4 weeks from randomisation; study drug will be continued for an additional 1 week. Surgery should occur as per local policies.If clinically necessary, surgery can be brought forward or not performed (this should be discussed with the Chief Investigator). The case should be presented to a multidisciplinary team meeting before any other non-surgical treatment is given. These patients will not be included in the analysis as, in the absence of surgery, it will not be possible to assess for post-treatment tissue markers.
Tissue Collection: Formalin Fixed Paraffin Embedded tissue will be taken from the radical prostatectomy specimen

Follow up 8–10 weeks post operativelyClinical assessments:Symptoms directed physical examination, including ECOG performance status, weight, waist/hip ratio and vital signsMedications reviewAdverse events and complete Clavien Dindo assessment
Laboratory determinations: Blood tests taken within 2 days of post-operative visit for other purposes can be used as part of the post-operative visit: FBC, renal function, LFT, bone profile, PSA, testosterone.

### Laboratory tests

Laboratory determinations including FBC, Renal function, LFT, bone profile, fasting glucose, PSA, testosterone, fasting lipid profile and HbA1c will be carried out by the local haematology and biochemistry laboratory at each site in accordance with local procedures.

Formalin fixed paraffin embedded tissue will be collected from baseline diagnostic biopsy and from the prostatectomy. Tissue will then be shipped to CMOP at DFCI. Samples will be processed and stored as per Laboratory Standard Operating Procedures.

The following analyses will be conducted at the CMOP on collected baseline and post-surgery tissue specimens:p-AMPK, p-ACC, FASN, ki-67 and TUNEL will be assessed in benign and malignant tissue by immunohistochemistry using image analysis.The ki-67 proliferation index is assessed by point counting 1000 cells, and is reported as percent positive cells.TUNEL is an apoptotic index defined as the number of apoptotic cells per 1000 tumour cells.Remaining markers will be measured using a H-score.

Methods for these analyses have been optimized and used in preliminary studies performed in collaboration at CMOP. Tissue (prostate) metformin concentrations will also be performed.

### Radiological assessment

During screening all five men undergoing 18F Choline PET/MRI will have successfully completed a MRI standard safety questionnaire (including eGFR) and their diagnostic clinical MRI will be have been checked to ensure it has visible disease. The patient will be asked to be nil by mouth 4 h prior the the scan. The scans will consist of:MRI Sequences: Prostate T1 and T2-weighted imagesprostate diffusion-weighted imagesBOLD MRI and MR spectroscopy.

Dynamic contrast enhanced MRI of prostate (0.1 mmol/kg IV). PET acquisition: 350 MBq 18F–choline IV. Dynamic image acquisition over pelvis. Patients will receive IV buscopan and undergo rectal filling as per standard MRI operating procedures.

### Dosing regimen

In order to limit gastrointestinal side effects patients will be instructed to take study drug at doses increasing from:500 mg once a day (day 1–2)500 mg twice a day (day 3–4)1 g twice a day from day 5 onwards for 4 weeks until prostatectomy +/− one week

Study drug will be continued until the evening prior to surgery. Placebo will be dose escalated in the same way. Participants will be given these instructions verbally as well as written instructions at the start of their medication compliance diary.

Study drug doses should ideally be taken at the same time each day. Missed doses of the study drug may be taken later, provided that the time of dosing is at least 6 h before the next scheduled dose. If dosing is missed for one day for any reason, double-dosing should not occur the following day. Acute alcohol intoxication can increase the likelihood of the rare, but serious adverse event of lactic acidosis. Therefore, all participants will be advised to avoid alcohol for the duration of the trial. Patients participating in the non-randomised 18F PET/MRI cohort will receive metformin, which will be dose escalated as outlined above. All dose modifications and duration of treatment will be identical to the randomized cohort.

### Dose reduction in case of adverse events

The investigator should determine if an adverse event is related to the study drug. Adverse events (AE) considered at least possibly related to study drug may require a dose reduction, a temporary hold (up to 7 days), or permanent discontinuation. Dose modifications should be based on the NCI CTCAE (version 4). Dose reduction for Grade 1 AEs is not required. Dose reduction for Grade 2 events should be considered only when the AE is judged by the investigator to be clinically intolerable. For Grade 3 and 4 AEs, the dose modification of study drug should follow the Dose Reduction Guidelines in the Tables 2 and 3 below. Dose modification for Grade 3 or 4 diarrhoea should follow the guidelines in Table 4 below.

**Table 2 Tab2:** General dose reduction guidelines

Grade I	Continue study treatment at same dose; monitor and treat as clinically indicated.
Grade II	Continue study treatment at same dose; monitor and treat as clinically indicated.
Grade III	Step 1. Interrupt study drug until toxicity reduced to ≤Grade 1. Step 2. Restart study treatment at same dose or lower dose at discretion of investigator
Grade IV	Step 1. Interrupt study drug until toxicity reduced to ≤Grade 2. Step 2. Restart study treatment at lower dose level.

**Table 3 Tab3:** Dose level dose

Dose level	Dose
0	1 g BD.
-1	500 mg BD
-2	Discontinuation

**Table 4 Tab4:** Dose reduction for specific toxicity: diarrhoea

Grade I	No action required.
Grade II	Concomitant anti-diarrhoeal agents may initially be administered without dose reduction. If Grade 2 diarrhoea persists, dose reduction should occur as per Table 2. Supportive care regimen should follow local standard of care.
Grade III	Dose reduction should occur as per Table 2.
Grade IV	Dose reduction should occur as per Table 2.

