### IMP risks

As Metformin is a licensed drug the reference document will be the Medley Pharma laboratories Summary of Product Characteristics (SmPC). The very common unwanted effects (less than or equal to 1 in 10) are gastrointestinal symptoms such as nausea, vomiting, diarrhoea, abdominal pain and loss of appetite.

Lactic acidosis is a rare, but serious, metabolic complication that can occur due to metformin accumulation. Reported cases of lactic acidosis in patients on metformin have occurred primarily in diabetic patients with significant renal failure. The incidence of lactic acidosis can and should be reduced by assessing other associated risk factors such as poorly controlled diabetes, ketosis, prolonged fasting, excessive alcohol intake, hepatic insufficiency and any condition associated with hypoxia. For full details please refer to the SmPC.

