### Withdrawal of patients

Participants have the right to withdraw from the study at any time for any reason. The investigator also has the right to withdraw patients from the study drug in the event of inter-current illness, AEs, SAE’s, SUSAR’s, protocol violations, administrative reasons or other reasons. It is understood by all concerned that an excessive rate of withdrawals can render the study un-interpretable; therefore, unnecessary withdrawal of patients should be avoided. Should a patient decide to withdraw from the study, all efforts will be made to report the reason for withdrawal as thoroughly as possible. Should a patient withdraw from study drug only, efforts will be made to continue to obtain follow-up data, with the permission of the patient.

Participants who wish to withdraw from IMP will be asked to confirm whether they are still willing to provide the following.trial specific data at their follow up visit

Patients who interrupt study drug for greater than 7 days, without the direction from their treating doctors, will be considered as non-compliant and will be discontinued from the study. These patients will be included in the safety assessments. They will be included in the pharmacodynamic, efficacy and safety assessments only if they received at least 21 days of treatment.

Treatment with study drug should be discontinued if it is considered to be in the best interest of the patient. Reasons for treatment discontinuation include:Disease progressionOccurrence of intolerable side effectsPatient withdrawal of consent or non-compliance.

Patients discontinued from the study for reasons unrelated to therapy, such as non-compliance, ineligibility or withdrawal of consent will be considered drop-outs. All of these patients are still evaluable for toxicity. Any subjects who withdraw prior to completing treatment will be replaced until 90 subjects in each of the randomized study arms have completed treatment.

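### Table 2 allows restart with more residual toxicity after a related Grade IV event (≤Grade 2) than after Grade III (≤Grade 1), and gives no reason

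*Protocol article*

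**What the plan says.** The section on dose reduction in case of adverse events covers events judged at least possibly related to study drug. Its opening text lists dose reduction, "a temporary hold (up to 7 days), or permanent discontinuation" as the possible responses. Grade 3 and 4 events are then to be handled by Tables 2 and 3.

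- **Table 2, Grade III:** "Interrupt study drug until toxicity reduced to ≤Grade 1", then restart at the same or a lower dose, as the investigator chooses.
- **Table 2, Grade IV:** "Interrupt study drug until toxicity reduced to ≤Grade 2. Step 2. Restart study treatment at lower dose level".
- **Table 3:** level 0 is 1 g twice daily, level -1 is 500 mg twice daily, and level -2 is discontinuation.
- **Table 4 (diarrhoea):** Grades III and IV are referred back to Table 2. For the milder grade: "If Grade 2 diarrhoea persists, dose reduction should occur as per Table 2".

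The section on withdrawal of patients adds a general rule: "Treatment with study drug should be discontinued if it is considered to be in the best interest of the patient". The per-protocol section counts a man as evaluable if he had at least 21 days at 1.5–2.0 g daily and no interruption in the 7 days before prostatectomy.

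**The concern.** A recovery threshold for restart would normally be at least as strict after a graver event as after a milder one. Here it runs the other way, in a table that is the written default for both grades. Diarrhoea, one of the very common unwanted effects of metformin, shows the consequence. A man with Grade IV diarrhoea may restart while it is still Grade 2, whereas a man with Grade III diarrhoea must wait until it is Grade 1. The first man restarts on the last active dose level, since the next step in Table 3 is to stop.

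The Risk/benefit section says "it is unlikely that patients will derive significant benefit by study participation". Re-exposure with Grade 2 toxicity still present therefore calls for a reason, and none is stated. What is at stake is the safety of the individual man, not the validity of the primary comparison.

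**Working it through.** **1. Does the restart dose explain the reversed thresholds?** The Table 2 rows give three restart paths:

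| Event | Restart dose | Recovery required |
|---|---|---|
| Grade III | 1 g twice daily | ≤Grade 1 |
| Grade III | 500 mg twice daily | ≤Grade 1 |
| Grade IV | 500 mg twice daily | ≤Grade 2 |

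The second and third paths have the same restart dose and differ only in the severity of the event. The graver event has the looser requirement, so the dose is not the explanation.

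**2. What would a stricter threshold cost the primary analysis?** The article states no figure to reproduce, so I counted combinations.

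Inputs:
- Full dose (2 g daily) starts on Day 5 (Dosing regimen).
- The only reduced level is 2 × 500 mg = 1 g daily (Table 3).
- A hold lasts at most 7 days (text above Table 2).
- The last dose is on the evening before surgery.
- Evaluability needs 21 days at 1.5–2.0 g daily and 7 uninterrupted days before surgery (Per protocol analysis).

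Let the event fall on day d ≥ 5, the hold last h = 1 to 7 days, and surgery be on day S, with restart by day S − 1. Before Day 5 the dose is at most 500 mg twice daily, so no lower active level exists and the restart rule does not arise.

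*Possible combinations for a given S.* For each h there are S − 5 − h event days. Summing over h gives 7(S − 5) − 28 = 7S − 63.
- S = 28: 7 × 28 − 63 = 133.
- S = 21 to 35: 7 × 420 − 15 × 63 = 2,940 − 945 = 1,995.
- S = 26 to 40: 7 × 495 − 945 = 3,465 − 945 = 2,520. This is the longest reading, with the four weeks counted from Day 5.

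*Combinations that stay evaluable.* Days at 1 g do not count, so all 21 qualifying days must precede the event: d − 5 ≥ 21, or d ≥ 26. Seven uninterrupted days before surgery require d + h ≤ S − 7. Since d + h is at least 27, S must be at least 34.

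| S | 34 | 35 | 36 | 37 | 38 | 39 | 40 |
|---|---|---|---|---|---|---|---|
| Evaluable | 1 | 3 | 6 | 10 | 15 | 21 | 28 |

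- Surgery on Day 28: 0 of 133.
- Surgery on Days 21–35: 1 + 3 = 4 of 1,995 (0.2%).
- Surgery on Days 26–40: 1 + 3 + 6 + 10 + 15 + 21 + 28 = 84 of 2,520 (3.3%), with at most 28 of 217 (12.9%) on Day 40.

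*Sensitivity.* Also counting events on Days 1–4, and events too late for a restart, enlarges the denominators and leaves the numerators unchanged. For surgery on Day 35 it gives 3 of 238 instead of 3 of 182. If the 1.5 g floor is read loosely, as a mean over at least 21 dosed days, the shares on these wider denominators are 6 of 196 (3.1%) for a last dose on Day 28, 30 of 245 (12.2%) on Day 35 and 44 of 273 (16.1%) on Day 39.

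On the literal per-day reading, these counts are a ceiling on what the fix could lose. A man drops out only if waiting for Grade 1 takes him out of the evaluable set.

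**The case against.** The strongest reply is that the protocol already tolerates Grade 2 toxicity on treatment. Table 2 continues Grade II events at the same dose, and the text considers reduction only when the event is clinically intolerable. A man restarted at Grade 2 after a Grade IV event takes half that dose. In the diarrhoea example he is already on the reduced dose that Table 4 would prescribe, so Tables 2 and 4 do not contradict each other. Nor is restart compelled: the tables are guidelines, permanent discontinuation is a listed option for any related event, and the withdrawal section requires stopping when that is in the man's interest.

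Much of this stands. It makes the point minor, and it rules out any claim that the protocol forces unsafe re-exposure. It does not explain why a man recovering from Grade III must reach Grade 1 at the same reduced dose while a man recovering from Grade IV need not. Discretion softens the written default without correcting it.

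A reader might also infer that restart after Grade IV is uniquely pointless for the primary analysis. The document does not support that. The loss of evaluability comes from any reduction to 1 g daily set against the 1.5 g floor, and a Grade III event restarted at the lower dose gives the same 4 of 1,995.

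**Conclusion.** The point holds as a minor per-patient safety correction: the Grade IV recovery threshold is looser than the Grade III one, without a stated reason, and the restart dose does not justify it. The effect on the primary result should be small. That rests on the judgement that Grade IV events are few, since the article gives neither their rate nor their timing. The counts weight every combination equally and are not probabilities.

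Three stronger readings are tempting and should not be drawn:

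- **That Grade IV must mean permanent discontinuation.** Nothing in the document requires it. It is a policy choice for the sponsor, and it would reduce drug exposure for the intention-to-treat and tissue-level analyses.
- **That a stopping rule for lactic acidosis is missing.** The IMP risks section defers to the product summary ("For full details please refer to the SmPC"), which is not shown, so no gap can be claimed.
- **That holds are open-ended.** The table cells say only that the hold lasts until recovery, but the text above them limits it to 7 days. The separate withdrawal rule, "Patients who interrupt study drug for greater than 7 days, without the direction from their treating doctors, will be considered as non-compliant", concerns undirected interruptions and does not alter that limit.

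**What to change.** In Table 2, change the Grade IV recovery threshold in Step 1 from ≤Grade 2 to ≤Grade 1, matching the Grade III row. Leave Step 2 (restart at the lower dose level) as it is, with the 7-day limit on holds still applying. If the sponsor prefers the present threshold, the reason should be stated. The dosing section applies the same dose modifications to the five PET/MRI patients, so the change covers them too.

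The cost is a protocol amendment to one table row, with no added patients, visits or procedures. A few men would restart later or not at all, and would have slightly less drug in tissue at surgery for the intention-to-treat and tissue-metformin analyses.
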